**Adult sample size**

The number of samples is obtained using the following relationship in each group:

$$n\geq2\frac{\left( z_{\alpha/2}+z_{\beta} \right)^{2} \sigma^{2}}{(\mu_{1}- \mu_{2})}$$

where the probability of type 1 error:

$$\alpha=0.05 \to z_{\alpha/2}=1.96$$

Probability of type II error:

$$\beta=0.10 \to z_{\beta}=1.28$$

$$1- \beta=0.90$$

Power of observed effect size:

$$\left( \mu_{1}- \mu_{2} \right)/{\sigma=0.75}$$

${\mu_{2},\mu}_{1}$indicate the average satisfaction score of the adults.

Minimum sample required:

$$n=2\left( 1.96+1.28 \right)^{2} \left( \frac{1}{0.75} \right)^{2} =37$$

At least 37 adults in each group should be considered for the research, and considering 40% attrition, the number of samples is 50 patients in each group.

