***Appendix No. 2:***

***Colonoscopy satisfaction questionnaire***

**Before colonoscopy**

1) Have you been seen as an outpatient by a doctor to discuss your condition and the planned catheterization procedure?

Yes, No

2) Has the doctor explained what is done during the colonoscopy procedure?

Absolutely, To Some Extent, No

3) During the pre-op clinic visit, were you told what to do after the colonoscopy?

Absolutely, To Some Extent, No

4) Have you been given enough information before the colonoscopy procedure?

Yes, No

5) Has the doctor or nurse explained what will be done during the procedure during the visit before the colonoscopy?

Absolutely, To Some Extent, No

6) Did you have unanswered questions about the procedure before being admitted to the hospital?

Yes, No

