**During colonoscopy**

7) If you were visited by a doctor in an outpatient clinic, how would you evaluate his visit?

Weak, good, not good, average, good, excellent, not usable

8) Did you have a chance to ask the remaining questions?

Yes, No

9) Did you feel ready for the operation?

Yes, No

10) Was your experience in the colonoscopy unit what you expected?

Yes, No

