**After colonoscopy**

11) After the operation, did one of the colonoscopy unit staff explain what happened?

Yes, No

12) When you left the colonoscopy unit, were you aware of the results?

Yes, No

13) Did you feel ready to be discharged when you left the hospital?

Yes, No

14) How satisfied were you with your experience when you left the hospital?

Not At All, Low, Moderate, Completely Satisfied, Very Satisfied

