**Discharge time from the hospital**

15) Did you have any complications as a result of your colonoscopy?

Yes, No

16) Would you recommend this hospital to others for colonoscopy?

Yes, No

1. :

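### Three items of the only outcome questionnaire are faulty as printed: item 1 names the wrong procedure, item 7's options cannot be ordered, and the top of item 14 is ambiguous

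*Protocol*

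**What the plan says.** Protocol, Research Method, makes satisfaction of colonoscopy patients the dependent variable. Under Adult sample size, the two means in the formula "indicate the average satisfaction score of the adults". Under Research tools and Data collection method, Appendix No. 2 is the only instrument that measures satisfaction. Appendix No. 1 is demographic.

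The relevant items of Appendix No. 2 are:

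- **Item 1** (Before colonoscopy): "Have you been seen as an outpatient by a doctor to discuss your condition and the planned catheterization procedure", answered yes or no.
- **Item 7** (During colonoscopy), a rating of the outpatient doctor's visit, with the options "Weak, good, not good, average, good, excellent, not usable".
- **Item 14** (After colonoscopy), satisfaction with the whole experience on leaving, with the options "Not At All, Low, Moderate, Completely Satisfied, Very Satisfied".

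Under Validity and reliability of tools, the protocol says that the questionnaires were assembled from several studies. It plans a review by ten faculty members, experts and nurses, with corrections to follow, and then Cronbach's alpha and test-retest. It states no rule for turning the 16 answers into a score.

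**The concern.** These faults lie in what the patient reads and ticks, before any scoring. A reverse-worded item can be re-keyed at analysis. A patient's answer about a procedure that was not planned cannot be reliably reinterpreted later. Nor can a tick at one of two identically labelled options, if the patient was judging by position. Since Appendix No. 2 supplies the only outcome, any error it adds goes straight into the comparison for which the trial is sized. The likely consequence is noise in the score and some loss of power. Nothing in the protocol suggests a bias towards either group.

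**Working it through.** **1. The items, read for order and content.**

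| Item | Printed | Problem |
|---|---|---|
| 1 | Names a catheterization | Wrong procedure for this study. A patient who reads it literally may answer no, whatever was discussed about the colonoscopy. |
| 7 | *Good* in second and fifth place, *not good* in third | No monotone order exists. The first *good* may be a full *good* or a low category wrongly labelled. Merging the two by label is right only in the first case. *Not usable* is not a grade at all. |
| 14 | *Completely Satisfied* fourth, *Very Satisfied* fifth | By position *very* is highest, but by meaning *completely* can be read as the maximum. |

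**2. How much of a score these items could carry.** The form has 11 yes/no items (1, 4, 6, 8 to 13, 15, 16), 3 three-level items (2, 3, 5) and 2 items with longer scales (7, 14). Assume one point per step and five real grades in item 7:

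- Total range = 11×1 + 3×2 + 2×4 = 25 points.
- Items 7 and 14 = 8/25 = 32%.
- With item 1 added, 9/25 = 36%.

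The protocol does not state this scoring. The calculation only shows that the faulty items need not be minor ones.

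**3. The plan's own figure.** Inputs from Adult sample size: z = 1.96 (α = 0.05), z = 1.28 (power 0.90), standardised effect 0.75.

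n = 2(1.96 + 1.28)² / 0.75² = 2 × 10.4976 / 0.5625 = 37.32. The protocol gives 37, so the figure reproduces to rounding.

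With power = Φ(d√(n/2) − 1.96):

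- n = 37: Φ(0.75 × 4.301 − 1.96) = Φ(1.266) = 0.897.
- n = 50: Φ(0.75 × 5 − 1.96) = Φ(1.79) = 0.963.

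**4. Illustrative size of the loss from items 7 and 14.** The assumptions, none of them in the protocol, are:

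- 16 items on one latent factor, summed.
- Item 7 coded by printed position, with half of the *good* answers at the first *good*.
- The top two grades of item 14 swapped.
- *Not usable* ignored, and item 1 taken as unaffected.

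The effect size without and with the two faults, under different loadings and item thresholds:

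- Loading 0.5, roughly even splits: 0.777 to 0.759, a loss of 1 − 0.759/0.777 = 2.3%.
- Loading 0.6: 0.727 to 0.706, a loss of 2.9%.
- Loading 0.4: 0.691 to 0.664, a loss of 3.9%.
- Loading 0.5, other thresholds: 0.710 to 0.660, a loss of 7.0%.

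(In the last three, items 6 and 15 were left unreversed in both values, so only the change is used.)

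Applied to the planned 0.75:

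| Loss | d | Power, n = 37 | Power, n = 50 |
|---|---|---|---|
| none | 0.750 | 0.897 | 0.963 |
| 2% | 0.735 | Φ(1.201) = 0.885 | Φ(1.715) = 0.957 |
| 7% | 0.6975 | Φ(1.040) = 0.851 | Φ(1.528) = 0.937 |

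**The case against.** **The validation step may catch this.** Reviewers will rate ambiguity, simplicity, relevance and necessity, and corrections are promised. A wrong procedure name or a doubled option is the kind of fault such a review looks for. That is fair, and it makes the correction cheap. But the listed criteria do not mention the order of response options, and test-retest can look good for a scale that is consistently misordered.

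**It may be a translation slip.** The English shows signs of translation, and the form patients receive may be sound. This cannot be checked from the protocol, whose appendix is the only version shown.

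**Scoring can absorb it.** If everyone who ticks either *good* means the same thing, coding by label recovers item 7 completely. Respondents may also take item 14's order from position. Both are possible, but neither can be verified once the answers are in. Printing a not-applicable option last is conventional; it only needs to be kept apart from the grades.

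**A stronger reading does not stand.** Items 6 ("Did you have unanswered questions about the procedure before being admitted to the hospital") and 15 ("Did you have any complications as a result of your colonoscopy") run against the other yes/no items. A reader might infer that the score will misrank patients, and that power at 37 per group falls from 89% to about 80%. The protocol does not support this. Mixed item direction is ordinary design, handled by keying, and the keying may be in an analysis plan not shown here. Nothing says item 15 enters the score. The 80% figure needs those two items left unreversed as well as items 7 and 14 coded by position. That is a hybrid: *Yes* and *Absolutely* are printed first, so a literal first-is-lowest coding would give them the low codes.

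**Conclusion.** The concern holds for items 1, 7 and 14, which are wrong or ambiguous as printed in the sole outcome instrument. It does not extend to items 6 and 15. Their direction is not an error, and they need only be keyed accordingly if they enter the score.

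The supportable consequence is that answers to the three items *may* be misread or misordered, with avoidable measurement error in the satisfaction score. The size cannot be derived from the protocol. The illustration for items 7 and 14, a 2% to 7% smaller effect, costs about 1 to 5 percentage points of power at 37 per group and about 1 to 3 at 50. It rests wholly on assumed loadings, thresholds and coding, and leaves item 1 out. The loss is probably modest. The case for acting is that the faults are plain, they sit in the only outcome, and later scoring cannot reliably repair items 1 and 7.

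**What to change.** Correct Appendix No. 2 at the validation step already planned, before the first patient completes it:

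- **Item 1:** replace catheterization with colonoscopy.
- **Item 7:** use one ordered set (weak, not good, average, good, excellent). Show not applicable separately and treat it as missing.
- **Item 14:** make the top two labels unambiguous, for example *Satisfied* and then *Completely satisfied*.
- Check the patient-language form against the corrected text, and ask the expert reviewers to look at response options as well as item wording.
- If items 6 and 15 enter the score, key them in the opposite direction to the other yes/no items.

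The cost is a few wording edits to a form that is still to be validated. No extra patients, visits or data are needed, and the sample size calculation is unaffected.

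### Items 3, 5 and 8 of the satisfaction questionnaire have no 'does not apply' answer, so inapplicable answers can be mixed with truly negative ones

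*Protocol*

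**What the plan says.** The form in Appendix No. 2 contains two filter questions, each answered Yes or No, and four questions that depend on them.

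- Visit filter, item 1: "1) Have you been seen as an outpatient by a doctor to discuss your condition and the planned catheterization procedure". Items 3 ("3) During the pre-op clinic visit, were you told what to do after the colonoscopy") and 5 ("5) Has the doctor or nurse explained what will be done during the procedure during the visit before the colonoscopy") follow. Each has three graded answers, the lowest being No.
- Question filter, item 6: "6) Did you have unanswered questions about the procedure before being admitted to the hospital". Item 8 follows: "8) Did you have a chance to ask the remaining questions". It is answered Yes or No.
- Item 7 also depends on a visit, but is worded conditionally: "7) If you were visited by a doctor in an outpatient clinic, how would you evaluate his visit". Its answer list is "Weak, good, not good, average, good, excellent, not usable", and the last entry reads as a not-applicable option.

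No skip instruction is printed after items 1 or 6. The Protocol gives no scoring key and no rule for inapplicable or blank items. The section on validity and reliability of tools treats the questionnaire as still to be validated and provides for corrections after expert review.

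**The concern.** Satisfaction is the study's dependent variable, and this form is the only instrument that measures it. Where a question does not apply and the form offers no way to say so, the patient must choose an answer that describes something else or leave a blank. The form deals with this at item 7 but not at items 3, 5 and 8, so it treats the same situation in two ways.

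Two things are at stake. At item 8, the share of patients with nothing left to ask is something education is likely to change, so the number of inapplicable answers may differ between groups because of the intervention itself. At items 3 and 5, the answer may reflect how the patient reached the unit and not how well the patient was served. That adds noise. It adds bias if the two groups differ in route of entry, which is possible because the Sampling section forms them purposefully and does not expressly list route of entry among the characteristics to be compared.

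**Working it through.** **Answer patterns, side by side.**

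| Pattern | What happened | What item 3 or 8 shows |
|---|---|---|
| Item 6 = No, item 8 = No | nothing left to ask | No |
| Item 6 = Yes, item 8 = No | questions, but no chance to ask | No |
| Item 6 = No, item 8 = Yes | nothing left to ask, chance existed | Yes |
| Item 1 = No, item 3 = No | possibly no visit at all | lowest category |

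The first two rows give the same item 8 record for different experiences. The third shows that a question-free patient is not forced into No.

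**Item 8, size.** The Protocol gives no item frequencies, so every input here is an assumption. Let p be the share with unanswered questions, c = 0.70 the share of those who got the chance to ask, and f the share of question-free patients who tick No. Assume that Yes is the favourable answer and that f is the same in both groups.

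- Intended favourable share, counting nothing left to ask as favourable: p·c + (1 − p).
- Share as printed: p·c + (1 − p)(1 − f).
- Between-group bias, education minus control: −f(p_control − p_education).

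With p = 0.60 in control and 0.30 in education, the intended shares are 0.42 + 0.40 = 0.82 and 0.21 + 0.70 = 0.91, a difference of +9 percentage points.

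| f | Control | Education | Difference (points) | Bias (points) |
|---|---|---|---|---|
| 0 | 0.82 | 0.91 | +9 | 0 |
| 0.25 | 0.72 | 0.735 | +1.5 | −7.5 |
| 0.50 | 0.62 | 0.56 | −6 | −15 |
| 0.75 | 0.52 | 0.385 | −13.5 | −22.5 |

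With 50% v 30% or 60% v 40%, the intended +6 becomes +1, −4 or −9, a bias of −5, −10 or −15 points. If item 8 is scored 0 or 1, the shift in the total score is therefore 0.05 to 0.225 (about 0.23) points.

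To scale this, assume a total of 21 points: 11 two-option items at 0-1 (11), three three-option items at 0-2 (6) and item 14 at 0-4 (4), with item 7 left out. Assume also a standard deviation of 2.5. The shift is then 0.05/2.5 = 0.02 to 0.225/2.5 = 0.09 standard deviations, against a planned effect of 0.75.

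**Item 8, a different target.** Suppose the quantity wanted is the Yes rate among patients who had questions, and write y = 1 − f. With 30% of controls and 60% of education patients question-free and c = 0.8, that rate is 80% in both groups. The printed rates, control v education, are 56% v 32% at y = 0, 71% v 62% at y = 0.5, 80% v 80% at y = 0.8 and 86% v 92% at y = 1. On this target the artefact runs against education when y < c, vanishes when y = c and favours education when y > c.

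**Item 3, size.** The plan's own figure first: 2 × (1.96 + 1.28)² / 0.75² = 2 × 10.4976 / 0.5625 = 37.3, which the Protocol gives as 37 per group. Now let a share r of patients have no visit and lose the full 2 points (2/21, about 10% of the total), independently of the rest of the score. The added variance is 4r(1 − r), and the effect becomes 0.75 × 2.5 / √(2.5² + 4r(1 − r)).

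| r | Effect | t-test power at 37 per group |
|---|---|---|
| 0 | 0.750 | 88.9% |
| 0.1 | 0.729 | 87.2% |
| 0.2 | 0.714 | 85.8% |
| 0.3 | 0.704 | 84.8% |
| 0.4 | 0.698 | 84.2% |

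This covers item 3 alone and takes the full loss from every affected patient. Item 5 is not in the calculation.

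**The case against.** A reader might infer that patients without a visit or without questions can only be recorded as dissatisfied, and that item 8 works against the education group. The Protocol supports neither statement. Item 8 asks about opportunity, so a patient with nothing left to ask can truthfully tick Yes, and any item can be left blank. No scoring key is printed, so the document does not show that No scores low. The direction at item 8 needs three things that it does not state: fewer remaining questions under education, some question-free patients ticking No, and No scoring lower. It also depends on the target chosen, as shown above. These objections stand.

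A second objection is that items 6 and 1, on the same form, can separate the cases through a scoring rule, which an analysis plan not shown here may contain. This stands only in part. Item 6 refers to the time before admission, and item 8 to whatever remained later. Item 1 asks about a doctor, while item 5 covers a doctor or nurse, so No at item 1 does not prove that there was no visit. A scoring rule can therefore recover only part of what the response options fail to record.

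Third, a change of sign at item 8 alone looks dramatic but is not a change of sign in the score. At 60% v 30%, item 6 contributes +30 points to education if its No is scored as favourable. Items 6 and 8 together then give +31.5, +24 or +16.5 points. This stands. So does the criticism of the item 3 figures: the Protocol describes 0.75 as an observed effect, so its standard deviation may already contain such variation.

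Finally, the planned expert review rates ambiguity and relevance and may catch the gap. That makes the review the right moment for the change, but nothing in its description points to inapplicable items.

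**Conclusion.** The concern holds in a limited form. Items 3 and 8, and similarly item 5, depend on circumstances that the form itself allows to be absent, and they lack the opt-out that item 7 appears to have. Inapplicable answers can therefore be mixed with negative ones in the study's outcome. The point is clearest at item 3, where No is the only literal fit for a patient who had no visit.

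At item 8, the benefit of education can be understated if all three conditions hold, f is similar in the two groups, and having nothing left to ask is meant to count as favourable. The size is unknown and probably small relative to the total score: 0.05 to 0.23 points of an assumed 21, and nothing if no question-free patient ticks No. The item 3 noise is likewise modest under its assumptions. This is a measurement flaw worth repairing before data collection; it does not invalidate the comparison.

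**What to change.** Make the change at the tool-correction step in the section on validity and reliability of tools, before the form is used.

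1. Add to item 8 an answer stating that the patient had no remaining questions, and count it as favourable. Alternatively, ask item 8 only when item 6 = Yes and score items 6 and 8 as one item.
2. Add to items 3 and 5 an answer stating that there was no such visit.
3. Treat those visit answers, and the last option of item 7, as not applicable.
4. Use item 1 as a filter and not as a scored item.
5. Rescale every scored item to 0-1, then average the applicable items.

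Steps 4 and 5 are needed because a plain mean of items with unequal ranges would still depend on route of entry. Suppose item 7 is scored 0-4. An otherwise perfect patient with a visit scores 25/16 = 1.56. One without a visit, with items 3 and 7 dropped and item 1 scored 0, gets (25 − 2 − 4 − 1)/14 = 18/14 = 1.29. Under the rule above, with item 8 kept separate, they score 15/15 and 12/12, both 1.00.

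The cost is three added response options and a short scoring rule, with no extra patients, visits or staff. The downside is that patients contribute slightly different numbers of items to the score.

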**After colonoscopy**

11) After the operation, did one of the colonoscopy unit staff explain what happened?

Yes, No

12) When you left the colonoscopy unit, were you aware of the results?

Yes, No

13) Did you feel ready to be discharged when you left the hospital?

Yes, No

14) How satisfied were you with your experience when you left the hospital?

Not At All, Low, Moderate, Completely Satisfied, Very Satisfied

**Discharge time from the hospital**

15) Did you have any complications as a result of your colonoscopy?

Yes, No

16) Would you recommend this hospital to others for colonoscopy?

Yes, No

1. :

